### 2.4. Risk Assessment

Screening for severe depression and suicidality is conducted as part of routine intake at the Women’s Health Concerns Clinic, prior to participants being screened for our study. These individuals would be identified as requiring acute intervention and excluded from the study’s recruitment and referred to appropriate clinical services. However, if imminent risk is identified during completion of the risk module of the Diagnostic Assessment Research Tool (DART), as part of the screening for the study, a safety planning process will be initiated by the assessor with the participant via Zoom. If a sufficient safety plan cannot be established, standard clinical escalation procedures will be implemented in accordance with the hospital’s protocols. Risk will be monitored throughout study participation, and all participants with a history of suicidality or current risk will be provided with crisis resources, including the Crisis Outreach and Support Team (COAST).

### 2.5. Study Arms

The 4-week mindfulness-based group intervention involves participating in a 4-week group that meets once a week, for 2 h. The session will be delivered through Zoom. Sessions will be delivered by a senior-level Ph.D. student in clinical psychology (ZB) and a clinical psychologist ([name], CP). Each session will consist of psychoeducation about anxiety during the perinatal period and mindfulness practices designed to foster a state of mindfulness and improve anxiety symptoms. To encourage daily practice, links to guided meditation (i.e., SoundCloud links) will be included in the mindfulness protocol shared with participants. The intervention protocol was adapted from existing evidence-based protocols, including the Mindfulness-based Cognitive Therapy for depression protocol [65], as well as other perinatal-specific protocols [25,50,52,55]. The content provided in each session is detailed in Table 1.

Intervention fidelity will be monitored using a session-level adherence checklist. A trained research assistant will be present for the full duration of each group session and will complete the checklist following each session to document adherence to core intervention components (e.g., psychoeducation content, mindfulness practices, and session structure). These procedures are intended to ensure the consistency of intervention delivery across sessions and groups.

The minimum attendance requirement is attending 3/4 sessions to be included in the primary analysis. In instances where a participant cannot attend a session, an individual make-up session will be delivered by one of the group facilitators. In addition to tracking attendance, recording of any technical disruptions related to virtual delivery will also be recorded.

Participants in the TAU control group will engage in TAU for 4 weeks (waitlist period), which entails continuing to meet with their healthcare practitioners on an as-needed basis. This includes meeting with their psychiatry team, attending regular evaluations within the hospital, and/or meeting with other allied health professionals such as social workers, nurses, or counsellors. The one restriction that is placed on the 4-week waitlist period is not engaging in any formal, structured psychotherapy (e.g., CB, DBT, or other mindfulness-based interventions). After the 4-week TAU period, participants will be given the option to complete the 4-week mindfulness intervention.

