### 2.12. Data Analysis

To determine condition differences on the self-report clinical outcomes, a series of repeated measures analysis of variance (ANOVAs) will be used. A two (experimental group vs. TAU group) by two (Time 1 vs. Time 2) repeated measures ANOVA will be used to examine differences. Further, in order to determine if benefits are maintained long-term, a within-subject repeated measures ANOVA will be conducted for the experimental group across three testing times (Time 1, Time 2, Time 2). The primary outcome (STICSA) will be evaluated at α = 0.05. All other self-report measures are secondary, pre-specified a priori, and Bonferroni correction will be applied to account for multiple comparisons where appropriate. Given the proof-of-concept nature of the study, findings from secondary outcomes will be interpreted cautiously. Partial eta-squared (η^2^) will be reported for ANOVA effects, and Cohen’s d with 95% confidence intervals will be calculated to inform future sample size calculations. Analyses will follow an intent-to-treat (ITT) approach, with missing data handled using appropriate methods (e.g., multiple imputation where assumptions are met). All analyses will be performed with IBM SPSS Statistics 23 [93].

Preprocessing of fMRI data will be conducted using a combination of SPM12 (http://www.fil.ion.ucl.ac.uk/spm/software/spm12; accessed on 22 November 2025), FSL (https://fsl.fmrib.ox.ac.uk/fsl/fslwiki/; accessed on 22 November 2025), and custom MATLAB (version R2025b) scripts. Preprocessing will include motion correction, coregistration to the structural image, spatial normalization, nuisance regression (motion parameters and white matter/cerebrospinal fluid signals), and temporal band-pass filtering. ROI-to-ROI functional connectivity analysis will be performed using SPM to evaluate changes in connectivity within the DMN and SN. A priori-defined regions of interest (ROIs) for the DMN include the medial prefrontal cortex and posterior cingulate cortex, and for the SN include the anterior insula and dorsal anterior cingulate cortex. Growth curve analyses will be conducted within a linear mixed-effects modelling framework to assess changes in resting-state functional connectivity over time. A linear mixed-effects model will be used to examine both within-subject changes over time (Time 1 vs. Time 2) and between-group differences (experimental group vs. CAN-BIND healthy controls).

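### Mindfulness is delivered in a few therapy groups, but the self-report ANOVAs treat participants as independent; any within-group correlation makes the standard error too small

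*Protocol article*

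**What the plan says.** **Delivery.** Section 2.5 describes the experimental treatment as a weekly group: "The 4-week mindfulness-based group intervention involves participating in a 4-week group that meets once a week, for 2 h". There is more than one group, because the fidelity checks are meant to "ensure the consistency of intervention delivery across sessions and groups". The number and size of the groups are not given. A missed session is replaced individually: "an individual make-up session will be delivered by one of the group facilitators". The TAU arm has no groups before Time 2; its participants are described as "continuing to meet with their healthcare practitioners on an as-needed basis", and mindfulness is offered to them only after the 4-week period.

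**Allocation and size.** Section 2.3 randomizes individuals 1:1. Section 2.2 sets a minimum of 20 per arm and recruits 25 per arm to allow for 20% attrition. No allowance for clustering is mentioned.

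**Analysis.** In Section 2.12, for the self-report outcomes, "a series of repeated measures analysis of variance (ANOVAs) will be used". The between-arm model is named: "A two (experimental group vs. TAU group) by two (Time 1 vs. Time 2) repeated measures ANOVA will be used to examine differences". STICSA is tested at 0.05. Maintenance is tested in one arm: "a within-subject repeated measures ANOVA will be conducted for the experimental group across three testing times". None of these models contains a therapy-group term. Cohen's d with a 95% interval is to feed later sample size calculations.

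**The concern.** Members of a therapy group share sessions, peers and discussion. Table 1 lists in-group practice in all four sessions and a check-in with home practice review from Session 2 on. Their outcomes may therefore be more alike than those of participants in different groups. One arm has this structure and the other does not, so the design is partially nested. Repeated measures ANOVA assumes independent participants in both arms.

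If there is positive correlation within groups, the mean of the mindfulness arm is less precise than the ANOVA takes it to be. Two results are affected: the primary p-value, and the interval for Cohen's d that the next trial is to use. The maintenance analysis is more exposed, because it uses only the clustered arm.

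**Working it through.** **The plan's own figure.** 20 / (1 − 0.20) = 25 per arm, 50 in total. This reproduces. No effect size, SD or power is stated, so there is no power figure to check.

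**Inputs.** From the article: 25 per arm, 1:1 allocation, alpha 0.05, one arm treated in groups. Assumed, because the article does not give them: group size m = 6 to 12, hence about 25/12 ≈ 2 to 25/6 ≈ 4 groups, and ICC 0.02, 0.05 or 0.10. The ICC that matters is that of the change score (or of the baseline-adjusted Time 2 score). Total variance is taken as equal in the two arms.

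**Test.** In a 2 × 2 repeated measures ANOVA the group-by-time F test is the square of the two-sample t test on change scores, so the t test can be studied directly.

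**Standard error.** The variance of the mindfulness-arm mean is multiplied by D = 1 + (m − 1)·ICC; that of the TAU mean is unchanged. With equal arms:

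true SE / naive SE = R = √[(D + 1)/2]

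understatement of the SE = 1 − 1/R

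| ICC | m | D | R | True SE larger by | Naive SE too small by |
|---|---|---|---|---|---|
| 0.02 | 6 | 1.10 | 1.025 | 2% | 2% |
| 0.02 | 12 | 1.22 | 1.054 | 5% | 5% |
| 0.05 | 6 | 1.25 | 1.061 | 6% | 6% |
| 0.05 | 12 | 1.55 | 1.129 | 13% | 11% |
| 0.10 | 6 | 1.50 | 1.118 | 12% | 11% |
| 0.10 | 12 | 2.10 | 1.245 | 25% | 20% |

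**Type I error, approximate.** The naive test rejects when |t| exceeds 2.011 (48 degrees of freedom). On the true scale that threshold is 2.011/R. The two-sided tail probabilities are 5.6–6.2% at ICC 0.02, 6.4–8.1% at 0.05 and 7.8–11.3% at 0.10.

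**Type I error, simulated.** Simulating the t test with 25 per arm, clustering in one arm and no true effect gives 5% at ICC 0. With 2 to 4 groups it gives about 5.5–6.4% at ICC 0.02, 6.4–8.5% at ICC 0.05 and 8.1–11.9% at ICC 0.10. A separate run of 200,000 trials per scenario with groups of 5 to 12 gives 5.2–5.5% at ICC 0.01, 6.2–8.2% at 0.05 and 7.3–11.4% at 0.10. The small differences come from how the 25 participants are split into groups.

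**Maintenance analysis.** With no unclustered arm to dilute the effect, the ratio is √D: 1.12–1.24 at ICC 0.05 and 1.22–1.45 at ICC 0.10. A one-sample test of change with n = 25 and groups of 5 to 12 serves as an illustration. It gives type I error of 7.4–11.1% at ICC 0.05 and 9.7–17.2% at ICC 0.10.

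**Can the trial estimate the group variance itself?** Take equal variance contributions from the two arms and k groups. The Satterthwaite degrees of freedom are then 4 / [1/(k − 1) + 1/24], which is 3.8, 7.4 and 10.7 for k = 2, 3 and 4. The critical t value alone widens the interval by about 40%, 16% and 10%, before any increase in the SE.

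**The case against.** The strongest reply is that the size of the problem is unknown and may be negligible. The article gives no ICC, group size or number of groups, and several features of Section 2.5 point to a low ICC. The same two facilitators deliver the sessions, a checklist is used to keep delivery uniform, missed sessions are replaced individually, and home practice uses recorded guidance. Individual randomization also means there is no group effect at baseline. This stands in part: it makes the low end of the range credible, but it does not show that the ICC is zero, since group members still share peers and discussion.

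A reader might infer that the 5% error rate is certainly lost. The documents do not support that: with no within-group correlation the rate is kept, and at ICC 0.01 the excess is at most about 0.6 percentage points. The top figure of about 12% needs both the largest assumed groups and the largest assumed ICC.

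A reader might also infer that every analysis in the trial ignores the groups. That goes too far. The exploratory connectivity outcome is analysed by a linear mixed-effects model whose random effects are not stated, so the point is confined to the self-report ANOVAs.

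Finally, a separate analysis plan could add a clustering adjustment, and this is a small proof-of-concept trial. The first part carries limited weight, because the article names the model and sets alpha for STICSA. The second explains why the remedy should be light, but the trial's interval for Cohen's d is expressly intended for later use.

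**Conclusion.** The point holds conditionally. The article fixes a model that assumes independent participants for an arm treated in a few groups. Whenever outcomes correlate positively within groups, the SE is too small and the primary and Cohen's d intervals are too narrow.

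Under assumed groups of 6 to 12, the SE is understated by about 6–11% at ICC 0.05 and 11–20% at ICC 0.10, with type I error of about 6–8.5% and 8–12%. The figures of 13% and 25% are the excess of the true SE over the naive one and should not be read as the understatement. At ICC 0.02 or below the effect is small. The maintenance test is affected more than the between-arm test.

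It would also be tempting to conclude that a partially nested mixed model must replace the ANOVA as the primary analysis. With about 2 to 4 groups that is not supported: the group variance would be too poorly estimated to carry the primary inference.

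**What to change.** 1. Record therapy-group membership for every mindfulness participant. Attendance is already tracked and a checklist is completed for each session, so this is one extra variable.
2. Analyse Time 2 STICSA with baseline STICSA as covariate. Baseline is already collected. This does not remove the clustering; it supplies the estimate and interval to which the next step applies.
3. Report the primary interval and the Cohen's d interval unadjusted, and again with the mindfulness-arm variance multiplied by 1 + (m − 1)·ICC at fixed ICCs such as 0.02, 0.05 and 0.10, with m the actual group size.
4. State that the unadjusted p-value assumes no within-group correlation, and say the same of the maintenance analysis.
5. If wanted, show a partially nested mixed model (random therapy-group effect in the mindfulness arm only, small-sample degrees of freedom) as supportive, with a note that the ICC estimate is very imprecise.

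The cost is revised analysis wording, a little more analysis work and a wider interval in the sensitivity rows. Recruitment, treatment and visits do not change.

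### The primary analysis set is defined two incompatible ways: section 2.5 admits only those attending 3 of 4 sessions, which can thin the mindfulness arm alone, while section 2.12 promises intent-to-treat

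*Protocol article*

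**What the plan says.** Section 2.5 (Study Arms) of the protocol article sets an entry condition: "The minimum attendance requirement is attending 3/4 sessions to be included in the primary analysis". The next sentence provides for missed sessions: "In instances where a participant cannot attend a session, an individual make-up session will be delivered by one of the group facilitators". It does not say whether a make-up session counts toward the three. The same section gives the control arm four weeks of usual care as a waitlist. The mindfulness sessions are offered to that arm only afterwards.

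Section 2.12 (Data Analysis) gives a different rule: "Analyses will follow an intent-to-treat (ITT) approach, with missing data handled using appropriate methods", with multiple imputation as an example. It mentions no per-protocol or completer set. The comparison of arms is described as follows: "A two (experimental group vs. TAU group) by two (Time 1 vs. Time 2) repeated measures ANOVA will be used to examine differences". On the error rate it says: "The primary outcome (STICSA) will be evaluated at α = 0.05".

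**The concern.** Attendance is observed after randomisation and exists in one arm only. If it decides who enters the primary analysis, the mindfulness arm is reduced to its adherent members while the TAU arm keeps everyone, including the mothers who would have attended poorly had they been offered the group. The arms are then no longer comparable by design. If low attenders tend to be the more distressed or burdened mothers, the group looks beneficial even when it does nothing.

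No other randomised evidence could make up for this. The Time 3 analysis is "a within-subject repeated measures ANOVA will be conducted for the experimental group across three testing times", and the imaging model compares the experimental arm with external healthy controls. Section 2.12 also intends Cohen's d to feed the sample size of a later trial, so any bias would carry over into that design.

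The contradiction is a problem in itself. With two primary populations on paper, the STICSA result could be reported under either, and the choice could be made after the data are seen.

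**Working it through.** **Do the two sections conflict?** Take a mother randomised to mindfulness who attends two sessions and completes the Time 2 questionnaires. Section 2.5 leaves her out of the primary analysis. Section 2.12 keeps her in. No sentence reconciles the two, and the word *primary* in 2.5 prevents reading the rule as belonging to a secondary set.

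**The plan's own figure.** Section 2.2 asks for at least 20 per arm and allows 20% attrition: 20 / (1 − 0.20) = 25 per arm, and 2 × 25 = 50 in total. This reproduces. The article gives no power, effect size or SD to check. The 20% is attrition, which is not the same as attending fewer than three sessions.

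**Who is analysed.** Under intent-to-treat, 25 + 25 = 50. Under the attendance rule, (25 − k) against 25, where k is the number of low attenders. If k were 5 (assumed, borrowing the 20%), the comparison is 20 against 25.

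**Bias when assignment has no effect.** Let p be the share who would attend fewer than three sessions, and let them improve d SD less than the others. Write m for the mean improvement of attenders.
- TAU, everyone kept: (1 − p)m + p(m − d) = m − pd
- Mindfulness, low attenders removed: m
- Spurious benefit: m − (m − pd) = p × d

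**Effect on the test.** The group-by-time test in a 2 × 2 repeated measures ANOVA is equivalent to a two-sample t-test on change scores. It was simulated under no effect with 25 randomised per arm, 20,000 runs, and a two-sided 5% level (the article does not state sidedness). Effects are in change-score SD units. All values of p, k and d are assumptions.

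Low attenders shifted by d and removed from mindfulness only:

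| p | d | Bias p × d (SD) | Type I error |
|---|---|---|---|
| 0.2 | 0.5 | 0.10 | 6.1% |
| 0.2 | 1.0 | 0.20 | 9.3% |
| 0.3 | 1.0 | 0.30 | 14.0% |

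A second run with more moderate inputs, fixing the number excluded and setting the gap between 0.25 and 0.75 SD:

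| Excluded of 25 | Bias (SD) | Type I error |
|---|---|---|
| 2 | 0.02 to 0.06 | 5.3% to 5.5% |
| 5 | 0.05 to 0.15 | 5.6% to 7.9% |
| 8 | 0.08 to 0.24 | 5.8% to 11.7% |

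Simulation error is roughly 0.15 to 0.25 percentage points: √(0.05 × 0.95 / 20,000) = 0.0015 and √(0.14 × 0.86 / 20,000) = 0.0025.

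**Hand check for 5 excluded and a 0.5 SD gap.** The standard error is √(1/20 + 1/25) = 0.30 SD and the bias is 0.10 SD, or 0.33 standard errors. The rejection rate is about Φ(−1.96 + 0.33) + Φ(−1.96 − 0.33) = 0.052 + 0.011 = 6.3%. The two simulations gave 6.1% and 6.5% for this case.

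**The case against.** The strongest reply is that section 2.12 governs the analysis and says intent-to-treat. If it prevails, nobody is dropped and there is no bias. That is right as far as it goes: exclusion is what 2.5 states, not a settled fact. But the document does not rank the two sections, so the primary population stays undefined until one of them is changed.

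Second, make-up sessions and the reminders in section 2.3 may leave few low attenders. This bears on size. With 2 of 25 excluded, the error rate hardly moves. It does not remove the rule.

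Third, the direction of the bias is assumed. Nothing in the article shows that low attenders fare worse. If mothers stop coming because they have improved, the bias runs against mindfulness. This also stands. The 14% figure needs the largest assumed share and the largest assumed gap together, and should be read as the top of a range.

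Fourth, this is a proof-of-concept trial, and a condensed article may leave detail to a fuller protocol or an analysis plan. Neither point settles the matter. The article commits to a test of its primary outcome at α = 0.05, and the problem is two written rules that disagree, not a missing detail.

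**Conclusion.** The concern holds. The protocol article gives two incompatible primary analysis populations. One of them conditions on a post-randomisation event that can occur only in the mindfulness arm, in the trial's sole randomised comparison. Following section 2.5 as written biases that comparison by the share excluded times the attender gap, unless the two groups change alike.

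The size cannot be derived from the documents. Across the assumed inputs the bias runs from 0.02 to 0.30 SD and the type I error from about 5.3% to 14%. It favours mindfulness if low attenders do worse and reverses if they do better. That the rule is wrong for a primary analysis does not depend on where in this range the truth lies. It should be corrected before outcome data are examined.

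**What to change.** Remove the attendance condition from section 2.5 as a rule for the primary analysis, and state in section 2.12, in words such as: *The primary analysis includes all randomised participants in their allocated arm regardless of the number of sessions attended, and Time 2 data are sought from all of them.* The second half largely confirms section 2.3, which already has both arms complete Time 2 questionnaires with no attendance condition.

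Keep attendance at 3 of 4 sessions as a labelled supplementary analysis, and say there whether make-up sessions count. A complier-average effect would be preferable to a simple per-protocol comparison because it respects randomisation, but with 25 per arm it will be imprecise. The main correction does not depend on that choice.

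The cost is two sentences of wording, with no change to recruitment, visits or the intervention. The primary estimate may be slightly less favourable.

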### 2.6. Neuroimaging Visits

During each imaging session at the IRC, participants will review an information sheet along with their completed screener with the imaging technician. Each imaging session will last approximately 20 min, during which participants will be instructed to keep their eyes open while focusing on a fixation cross. As research scans are not intended for diagnosis, if an abnormality is seen on an MRI scan, no formal report will be issued, and participants will be advised to consult with their family doctor/general practitioner.

The attained images will later be compared to healthy control fMRI data from the Canadian Biomarker Integration Network in Depression (CAN-BIND), a standardized research platform that collects comprehensive data from both healthy and clinical samples. CAN-BIND data are comparable in terms of core MRI acquisition protocols; however, as historical control data, these comparisons may be influenced by unmeasured factors such as differences in resting-state instructions, time-of-day effects, and residual demographic or contextual mismatches, and are therefore interpreted as exploratory.

### 2.7. Participation Time Commitment

Total participation time for the experimental group is approximately 13–15 h across the 4-week intervention and follow-up period. This includes four 2 h virtual group sessions (8 h), completion of self-report questionnaires at three time points (piloting indicated that Time 1 requires approximately 15–20 min, as many measures are already part of the GPD [see page 5], and Time 2 and Time 3 each require less than 30 min; ~1–1.5 h total), two MRI sessions of approximately 20 min each (approximately 1 h including preparation), and strongly encouraged home mindfulness practice (recommended 10–20 min per day, flexible in timing). Participants in the TAU group complete approximately 1–1.5 h of questionnaire-related activities across two time points. As indicated, the participants will be compensated for all questionnaire and scan completions. Compensation is structured to acknowledge time and inconvenience rather than to function as an inducement. The compensation rates are consistent with those used in local perinatal mental health and neuroimaging research, including those in our research group, and were approved by the institutional Research Ethics Board.

